## Abstract

**Background::**

Anal fistula is a common anorectal disease. So far, operation is still the optimal method to cure anal fistula. High anal fistula (HAF) is an even more clinically difficult disease to treat. Evidence suggested that seton placement can be a definitive treatment for HAF. However, tightening the seton brings great pain to patients, which affects the clinical application of the therapy. Also, this may lead to difficulty in controlling anal fluids and gas because of the larger scar left and the local defect in the anal after the operation. We propose an innovative seton technique for the treatment of HAF, after long term attempts, the operation of the modified seton cutting technique. The aim of our present study is to compare the difference of anal function, healing time, pain severity, recurrence, and complications between the procedure of the modified seton cutting technique and the conventional cutting seton operation against HAF with a randomized, controlled, prospective study.

**Methods::**

204 participants in this trial will be randomly divided into treatment group (procedure of the modified seton cutting technique) and control group (cutting seton technique) in a 1:1 ratio. The outcomes of continence state, pain severity after tightening, complete healing of fistula, duration to healing, operation time, recurrence rates, and postoperative complications will be recorded at 1, 2, 3, 4 weeks, then every month in the outpatient clinic. Data will be analyzed by SPSS version 22.

**Conclusions::**

The findings of the study will help to explore the efficacy and safety of the procedure of the modified seton cutting technique against AF.

**Trial registration number::**

DOI 10.17605/OSF.IO/V6G2S

## Introduction

1

Anal fistula is a common anorectal disease, with an estimated prevalence of 0.2%.^[1]^ It is often followed with an infection that does not easily heal with medications alone. So far, operation is still the optimal method to cure anal fistula. High anal fistula (HAF) is 1 of the intractable diseases in colorectal surgery, and it is difficult to achieve both goals of eradicating anorectal sepsis and preserving anal function. In recent years, more and more sphincter-sparing techniques have been applied to the treatment of HAF, including seton,^[2,3]^ endoanal advancement flap,^[4]^ ligation of intersphincteric fistula tract,^[5,6]^ and video-assisted anal fistula treatment.^[7]^ Nevertheless, those techniques may result in high recurrence rates.^[8,9]^

Evidence suggested that cutting seton technique can be a definitive treatment for HAF.^[10,11]^ The mechanism by which a drainage seton acts is still not clear, but by chronic strangulation, drainage, and stimulation, the technique can preserve the anal function as much as possible. However, the traditional cutting seton technique often needs 2 or even several times to tighten the thread. Because of the abundant nerves in the anal region, tightening the seton brings great pain to patients, which affects the clinical application of the therapy. In addition, it may lead to difficulty in controlling anal fluids and gas because of the larger scar left and the local defect in the anal after the operation.

Therefore, we propose an innovatively modified seton cutting technique for the treatment of HAF after long term attempts. In the procedure, a drainage seton is rerouted around internal anal sphincter to divide it slowly in the first stage, then loosely tighten the seton to promote the fibrosis of the anorectal ring when the granulation tissue grows close to the seton area in the middle stage, and incised the anorectal ring with a scalpel at last. The procedure could significantly reduce the pain when tightening the seton, shorten the healing time, and effectively shrink the scar, and preserve the anal function. The aim of our present study is to compare the difference of anal function, healing time, pain severity, recurrence, and complications between the procedure of the modified seton cutting technique and the conventional seton cutting technique against HAF with a randomized, controlled, prospective study.

## Methods

2

### Study design

2.1

This is a single-center, randomized, and controlled clinical trial. It has been registered in open Science Framework (Registration number: DOI 10.17605/OSF.IO/V6G2S), and approved by the Ethics Committee of Changshu Hospital Affiliated to Nanjing University of Chinese Medicine, and it will be carried out in accordance with the Declaration of Helsinki. The study conforms to the Standard Protocol Recommendations for Interventional Trials 2013 Statement,^[12]^ and the results will be reported according to the CONSORT Statement extension for trials.^[13]^

### Participants

2.2

Participants will be mainly recruited from inpatients of proctology department in Changshu Hospital Affiliated to Nanjing University of Chinese Medicine. Patients are included if they meet the following criteria:

(1)Patients meeting the diagnostic criteria for AF(2)Patients aged from 18 to 70 years old;(3)Patients without obvious deformity of anus before the operation;(4)Patients confirmed to high anal fistula by intra-anal digital examination and probe examination, intracavitary B ultrasound or pelvic MRI;(5)Written informed consent.

Patients are excluded if they present the following criteria:

(1)Patients who have undergone AF surgery 2 or more times;(2)AF due to trauma, tuberculosis, Crohn, ulcerative colitis;(3)Patients with rectal cancer, rectal polyps, and other anorectal diseases.(4)Women in pregnancy, lactation and menstruation.

### Randomization and blinding

2.3

The patients will be randomly divided into treatment group and control group in a 1:1 ratio by a computer-generated randomization list (Fig. 1). Blind method is not applicable because of different operations, and an independent professional researcher will analyze the statistic who does not know the identification of the groups.

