#### Intervention group

2.4.1

The procedure of the modified seton cutting technique will be performed with the following procedure:

(1)Make sure the position of internal ostium and the path of the fistula and its relationship with the sphincter by digital examination combined with preoperative intracavitary B-ultrasound or MRI;(2)From the posterior triangular approach of the anal canal, under the guidance of the probe, incise the skin and subcutaneous tissue along the fistula canal 2 cm above the anal margin to expose the posterior rectal space;(3)Explore the internal ostium and place a rubber seton, and tight the seton after the operation;(4)Properly trim the edge of the skin to maintain smooth drainage, and completely stop bleeding;(5)After the operation, when the granulation tissue grows close to the seton area, slightly tighten the seton and then hang it on the wound surface. After the granulation tissue growing close to the seton area again and the area becoming fibrosis, and the second formation of the anorectal ring, directly incise the seton area under local anesthesia.

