#### Control group

2.4.2

Cutting seton technique will be performed with the same procedure with the following procedure:

(1) to (4): The first 4 steps are the same with that in treatment group

(5) After the operation, when the granulation tissue grows close to the seton area, tighten the seton once and every 7 days according to the patient's tolerance to pain and the operator's clinical experience, until the rubber band falls off and the tissue is completely cut.

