### Outcome variables

2.5

The primary outcomes of the study are the continence state after surgery as assessed with Wexner incontinence score,^[14]^ and pain severity after tightening by Visual Analogue Scale. Secondary outcomes include complete healing of fistula, duration to healing, operation time, recurrence rates, and postoperative complications. All possible adverse events will be recorded, such as bleeding, anal stenosis, anal fissure, urinary retention, difficulty in defecation, urgency of stool, pelvic sepsis at any time. Patients will be followed-up at 1, 2, 3, 4 weeks, then every month in the outpatient clinic. At 6 months postoperatively, patients will be clinically assessed for recurrence of AF.

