## Discussion

3

At present, in the surgical treatment of HAF, cutting seton drainage is still the main surgical procedure. By cutting the sphincter slowly with the unique elastic cutting action of the seton, it could induce inflammatory fibrosis, avoid the sphincter retraction and separation, and prevent anal incontinence when the sphincter is momentarily severed.^[11]^ However, there are still some shortcomings according to literature reports.^[16,17]^ First, the pain in the treatment process is severe, because of continuously cutting the fistula and the anal sphincter by the elastic seton. Second, the healing time is longer, which needs about 40 to 50 days. Third, the left scar is large and obvious, which will affect the function of the anal sphincter, leading to incomplete anal incontinence.

The operation of the modified seton cutting is a modified technique of the conventional cutting seton, which could weaken the effect of chronic cutting. The modified technique is supposed to increase the cure rate, reduce the severe pain during the postoperative seton-tightening process, reduce local inflammation and scar, and shorten the healing time. Therefore, we try to conduct a clinical trial to compare the difference of anal function, healing time, pain severity between the procedure of the modified seton cutting technique and the conventional seton placement technique against HAF. However, we need to address several limitations in this protocol. First, the evaluator-blinded-only trial may lead to certain biases. Second, being a single institution study may affect the conclusions.

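### The stated blinding status is inconsistent: the Methods mask only the data analyst, the Discussion says evaluator-blinded, and the reason given for not blinding does not cover the shared steps 1 to 4

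*Protocol article*

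**What the plan says.** Section 2.3 (Randomization and blinding) gives one reason for not blinding: "Blind method is not applicable because of different operations". It then provides a single safeguard: "an independent professional researcher will analyze the statistic who does not know the identification of the groups".

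Section 2.4.2 (Control group) says of the control procedure: "The first 4 steps are the same with that in treatment group". The arms part at step 5, which both arm descriptions place after the operation. In the modified arm the seton is slightly tightened once the wound has granulated, and later the operator is to "directly incise the seton area under local anesthesia". In the control arm the instruction is to "tighten the seton once and every 7 days according to the patient's tolerance to pain and the operator's clinical experience", until the band drops off.

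Section 2.5 (Outcome variables) names two primary outcomes: the "continence state after surgery as assessed with Wexner incontinence score", and pain after tightening on a visual analogue scale (VAS). The five secondary outcomes are complete healing, time to healing, operation time, recurrence and complications. For recurrence it adds: "At 6 months postoperatively, patients will be clinically assessed for recurrence of AF". It does not say who scores or judges any of these.

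The Discussion (Section 3) lists as its first limitation that "the evaluator-blinded-only trial may lead to certain biases".

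**The concern.** Two statements do not fit together. The Methods say that blinding does not apply and mask the analyst. The Discussion says that the evaluator is blinded. Under the CONSORT reporting to which Section 2.1 commits the trial, a reader will take evaluator-blinded to mean that outcomes were assessed by someone unaware of the arm. A masked analyst is a different safeguard: that person receives scores already recorded and cannot undo any influence on how they were recorded.

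The reason for not blinding is also broader than the procedures support. If the operation is the same up to the end of step 4, the surgeon has no stated need to know the arm while performing it. Operation time is a secondary outcome. Knowing the arm during a shared operation is therefore an avoidable route to a difference in that outcome and in how the operation is carried out.

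The Introduction already expects less pain, faster healing and better preserved function with the modified technique, so any expectation among those who operate or assess leans one way.

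**Working it through.** The point rests on no figure, and the fix alters none. The plan's sample size is in order for this purpose. With 25.5% versus 10%, two-sided α = 0.05, power 80% and unpooled variance, n = (1.960 + 0.842)² × (0.255 × 0.745 + 0.10 × 0.90) / 0.155² = 91.47, so 92 per group as Section 2.6 states. The rest of the check is a comparison of the text.

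**Step 1. Who is masked?**

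| Role | Section 2.3 | Sections 2.4–2.5 | Discussion |
|---|---|---|---|
| Patient | blinding not applicable | step 5 differs visibly | not masked (evaluator only) |
| Surgeon, index operation | blinding not applicable | steps 1–4 the same | not masked (evaluator only) |
| Staff delivering step 5 | blinding not applicable | must know the arm | not masked (evaluator only) |
| Outcome assessor | no masking provided | not identified | masked, if this is the evaluator |
| Data analyst | masked | – | masked, if this is the evaluator |

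If evaluator means the outcome assessor, the Discussion names a safeguard that the Methods do not set up. If it means the analyst, the Discussion uses the wrong label. Neither reading leaves both sections correct as written.

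**Step 2. Does the stated reason hold for each role?** For patients and for staff delivering step 5 it does: one arm has repeated tightening, the other a late incision under local anaesthesia, and neither can be disguised. For the surgeon during steps 1 to 4 it does not, because Section 2.4.2 declares those steps common to both arms. For an outcome assessor who takes no part in step 5, a difference between procedures is not in itself a reason against masking.

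**Step 3. Is the operation really shared?** Section 2.4.2 says so without qualification. The Introduction, describing the modified technique, speaks of a first stage in which a draining seton is led round the internal sphincter so as to divide it gradually. That could be read as specific to the modified arm. The two passages have to be reconciled before anyone relies on the operation being identical; the article does not settle which governs.

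**Step 4. Which outcomes are exposed, and to whom?**
- Operation time: to the surgeon's knowledge of the arm. This assumes that it means the index operation; the article does not say whether the later incision counts.
- Wexner score: to whoever scores it, and to the patient's own expectation where the answers are the patient's.
- Complete healing, time to healing and recurrence: to the examiner's judgement.
- VAS pain: mainly to the patient's expectation. A masked assessor would protect it little.

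**The case against.** The strongest reply has four parts.

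First, the Discussion raises blinding as a weakness. A reader might infer that the article claims a protection it lacks. The text does not support that: evaluator may be loose wording for the masked analyst, and the sentence concedes bias. This is a mislabelling. It still stands as one, because the label would be read differently in a trial report.

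Second, this is a condensed article. Who collects each outcome, and whether that person is masked, may be set out in the full protocol. A reader might infer that the trial has no masked assessor; the article shows only that none is described. What stands is the conflict between two things the article does state.

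Third, a reader might conclude that the stated reason for not blinding is simply false. It is not. Step 5 belongs to the technique and differs visibly, so the reason is sound for patients and for the staff treating them. It fails only for the shared steps and for an independent assessor.

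Fourth, masked assessment has limits here. The article does not mention uninvolved staff who could do it. The modified technique is expected to leave a smaller scar, which may reveal the arm to an examiner. Patient-rated outcomes gain little. All of this is right, and it is why masked assessment is not demanded below.

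It is also tempting to express the risk as a number of misjudged patients against the assumed 15.5-point difference in incontinence (25.5% minus 10%). Any such number would be arbitrary, and Section 2.5 names a Wexner score without a cutoff for incontinence, so no size can be given.

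**Conclusion.** The point holds in a limited form. Section 2.3 and the Discussion describe the blinding differently and must be reconciled. The reason given in Section 2.3 is valid for patients and for those delivering step 5, but it does not extend to the index operation.

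The consequence is qualitative: no sample size, endpoint or test changes. The outcomes that better arrangements could protect are operation time and, if an assessor is masked, the scoring of Wexner and the judgements of healing and recurrence. VAS pain and patient-reported continence remain open to expectation whatever is done.

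The conclusion about the surgeon assumes that Section 2.4.2, and not the Introduction's account of a first stage, describes what is done in the operation. The conclusion about the label needs no assumption.

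**What to change.** 1. Reconcile the Introduction's description of the first stage with the statement in Section 2.4.2 that the first four steps are common to both arms. If they are common, state in Section 2.3 that the allocation is not disclosed to the surgeon until step 4 is complete. Operation time and the conduct of the shared operation then cannot depend on the arm. Cost: small theatre logistics, since someone other than the surgeon must hold the allocation until then.

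2. In the Discussion, replace the evaluator-blinded label with open-label, analyst-blinded. The exception is if the Wexner, healing and 6-month recurrence assessments are in fact made by existing staff who are not told the arm; in that case Section 2.3 should say so and name the outcomes covered. Cost: wording only.

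3. Limit the stated reason in Section 2.3 to patients and staff delivering step 5. Add to the limitations that VAS pain and patient-reported continence are open to patient expectation, and that scar differences may unmask an examiner. Cost: two sentences.

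None of this alters either surgical procedure, the endpoints or the 204 patients planned.

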**Figure 1 F1:**
[figure not shown]
Flow diagram of the study.

### Interventions

2.4

Before the operation, patients will get blood routine test, blood glucose, coagulation, liver and kidney function, infectious disease test series, and electrocardiogram. Intraspinal anesthesia will be performed.

Before the operation, patients will get blood routine test, blood glucose, coagulation, liver and kidney function, infectious disease test series, and electrocardiogram. Intraspinal anesthesia will be performed.

#### Intervention group

2.4.1

The procedure of the modified seton cutting technique will be performed with the following procedure:

(1)Make sure the position of internal ostium and the path of the fistula and its relationship with the sphincter by digital examination combined with preoperative intracavitary B-ultrasound or MRI;(2)From the posterior triangular approach of the anal canal, under the guidance of the probe, incise the skin and subcutaneous tissue along the fistula canal 2 cm above the anal margin to expose the posterior rectal space;(3)Explore the internal ostium and place a rubber seton, and tight the seton after the operation;(4)Properly trim the edge of the skin to maintain smooth drainage, and completely stop bleeding;(5)After the operation, when the granulation tissue grows close to the seton area, slightly tighten the seton and then hang it on the wound surface. After the granulation tissue growing close to the seton area again and the area becoming fibrosis, and the second formation of the anorectal ring, directly incise the seton area under local anesthesia.

#### Control group

2.4.2

Cutting seton technique will be performed with the same procedure with the following procedure:

(1) to (4): The first 4 steps are the same with that in treatment group

(5) After the operation, when the granulation tissue grows close to the seton area, tighten the seton once and every 7 days according to the patient's tolerance to pain and the operator's clinical experience, until the rubber band falls off and the tissue is completely cut.

### Outcome variables

2.5

The primary outcomes of the study are the continence state after surgery as assessed with Wexner incontinence score,^[14]^ and pain severity after tightening by Visual Analogue Scale. Secondary outcomes include complete healing of fistula, duration to healing, operation time, recurrence rates, and postoperative complications. All possible adverse events will be recorded, such as bleeding, anal stenosis, anal fissure, urinary retention, difficulty in defecation, urgency of stool, pelvic sepsis at any time. Patients will be followed-up at 1, 2, 3, 4 weeks, then every month in the outpatient clinic. At 6 months postoperatively, patients will be clinically assessed for recurrence of AF.

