### Sample size calculation

2.6

According to previous literature^[15]^ that reported fecal incontinence to occur in up to 25.5% of patients with AF after cutting seton technique. Presuming that the rate of fecal incontinence after the operation of the modified seton cutting technique will be 10%, and taking α of 0.05 and β of 0.2, a sample size of 92 in each group will be needed. In order to compensate for loss to follow-up, 204 patients will be ultimately included.

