### Statistical methods

2.7

Data will be analyzed by SPSS version 22(Created by IBM Corporation, New York, America). Statistical testing is 2-sided and *P* < .05 is considered statistically significant. Continuous data are expressed in of mean ± standard deviation, or median (quartile), and categorical variables as number and percentage. Student *t* test will used for normally distributed data and Mann–Whitney *U* test for non-normally distributed data. Fisher test or Chi-squared test will be used to analyze categorical data.

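### Two primary outcomes, each tested at two-sided 0.05 with no rule linking them: if either one can support a positive claim, the chance of a false positive is up to 9.75%, not 5%

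*Protocol article*

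**What the plan says.** Three sections of the protocol article bear on this.

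- **Section 2.5, Outcome variables**, lists two primary outcomes: "The primary outcomes of the study are the continence state after surgery as assessed with Wexner incontinence score", "and pain severity after tightening by Visual Analogue Scale". Neither is ranked above the other.
- **Section 2.7, Statistical methods**, gives one threshold for everything: "Statistical testing is 2-sided and *P* < .05 is considered statistically significant". It mentions no ordering, split or adjustment.
- **Section 2.6, Sample size calculation**, works on one of the two outcomes only. It cites literature that "reported fecal incontinence to occur in up to 25.5% of patients with AF after cutting seton technique", presumes 10% with the modified technique, and concludes: "taking α of 0.05 and β of 0.2, a sample size of 92 in each group will be needed". The total is then raised to 204 for loss to follow-up. There is no calculation for pain.

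No section states a success rule, whether either outcome or both.

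**The concern.** With two primary outcomes, a trial needs a rule for what counts as a positive primary result. Without one, a reader who applies section 2.7 literally can call the trial positive on whichever outcome falls below 0.05. A pain-only result could then be presented as a positive primary finding although the incontinence comparison, the only one the trial was sized for, had failed. The chance of such a claim when neither outcome truly differs would exceed 0.05.

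The opposite reading, that both must succeed, protects the error rate but leaves the stated power without support. So the choice changes what the trial's error rates mean, and it is credible only if made before outcome data are seen.

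**Working it through.** **Inputs from the protocol article**
- Incontinence 25.5% (control) and 10% (modified technique), α = 0.05, β = 0.2, 92 per group, 204 in total: section 2.6.
- 1:1 allocation: section 2.3.
- Two primary outcomes: section 2.5. One two-sided 0.05 threshold: section 2.7.

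**Assumption.** The correlation between the two test statistics is not given, so a range from 0 to 0.9 is shown.

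**1. Reproduce the 92 per group.** Two proportions, unpooled variance:

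n = (z₀.₉₇₅ + z₀.₈₀)² × [p₁(1−p₁) + p₂(1−p₂)] / (p₁−p₂)²

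= (1.960 + 0.842)² × [0.255×0.745 + 0.10×0.90] / 0.155²

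= 7.849 × 0.279975 / 0.024025 = 91.5, rounded up to 92.

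The arcsine formula gives 91.06, also 92. The pooled formula gives 95, and 107 with continuity correction. So the stated figure is the usual one with the full two-sided 0.05 placed on incontinence. Nothing was reserved for pain.

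**2. Error rate if either outcome suffices.** With independent tests:

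1 − (1 − 0.05)² = 1 − 0.9025 = 0.0975.

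With correlated, jointly normal test statistics it is 1 − P(|Z₁| ≤ 1.96 and |Z₂| ≤ 1.96):

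| Assumed correlation | At least one false positive |
|---|---|
| 0 | 9.75% |
| 0.3 | 9.5% |
| 0.5 | 9.1% |
| 0.7 | 8.3% |
| 0.9 | 7.0% |

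Independence is the worst case here, and the general Bonferroni bound is 10%. Counting only false positives that favour the modified technique, independence gives 1 − 0.975² = 4.9% against 2.5%, a similar ratio.

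**3. Error rate and power if both are required.** A false claim then needs a false positive on at least one outcome that truly does not differ, so its probability is at most 0.05. The power for success cannot exceed the power of either component. The 80% for incontinence is therefore an upper limit, and the power for pain is not given.

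**4. What each remedy does to power for the incontinence rate at 92 per group.** Unpooled formula:

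0.155 / √(0.279975/92) = 2.810.

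- At α = 0.05: Φ(2.810 − 1.960) = 80% (pooled formula 79%). A fixed sequence that starts with incontinence keeps this.
- At α = 0.025: Φ(2.810 − 2.241) = 71.5% (pooled formula 69.9%).

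Restoring 80% under a 0.025 split needs 111 per group by the unpooled formula (115 pooled). The step from 184 to 204 implies a loss of 1 − 184/204 = 9.8%. With that loss, 111/(184/204) is about 124 per group, or 248 in total, against 204 planned.

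**The case against.** The strongest reply is that the article never says either outcome is enough. It joins the two with a conjunction and describes its aim as comparing several outcomes. If both were meant to be necessary, the type I error is not inflated. That stands, and it is why the 9.75% must be stated conditionally. A reader might infer that the trial's false-positive rate simply is nearly double. The document does not support this, because no success rule is written in either direction.

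A reader might also take the 5% as a trial-wide guarantee that is being broken. It is not presented that way. In section 2.6 it belongs to one comparison of incontinence rates, and in section 2.7 it is a per-test threshold.

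It is also tempting to say that pain is the easier outcome to win because it is unblinded. Section 2.3 rules out blinding because the operations differ, which affects both outcomes, and the Discussion calls the trial evaluator-blinded only. No VAS effect size, standard deviation or power is given, so relative ease cannot be derived.

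Finally, this is a condensed article, and a multiplicity rule may sit in an analysis plan not shown. A hierarchy there would be compatible with sections 2.6 and 2.7, and an absent rule would not be a finding by itself. What remains is that this document itself fixes two unranked primaries, one unadjusted threshold for all tests, and a sample size that uses all of α on one of them. Applied as stated, these let a pain-only result pass as primary, and an α split elsewhere would contradict section 2.6.

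**Conclusion.** The concern holds in conditional form. If a significant result on either primary supports a positive claim, the chance of at least one false positive is up to 9.75%, and still about 7.0% at an assumed correlation of 0.9. If both are required, it is at most 5%, and 80% becomes a ceiling on the power for trial success. A written rule is needed on either reading.

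These figures count one test per outcome. Section 2.5 lists visits at weeks 1 to 4 and then monthly without fixing one assessment time for either primary, so they assume that a single time is chosen for each.

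A reader might also infer that a fixed sequence preserves 80% power for the Wexner score. It does not follow: section 2.5 names the score, but section 2.6 powers a binary incontinence rate, and no threshold connects them. The 80% is established for the rate only.

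**What to change.** State a fixed sequence in sections 2.5 and 2.7:

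1. Test continence first at two-sided 0.05, using the fecal incontinence rate on which the 92 per group is based. Define incontinence from the Wexner score and name one assessment time.
2. Test VAS pain after tightening as confirmatory at two-sided 0.05 only if the first test is significant. Otherwise report pain descriptively. Name its assessment time too.
3. State that the primary claim rests on continence.

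This holds the error rate across the two primaries at 0.05, needs no extra patients, and keeps the planned 80% power for the incontinence rate. An α split or a both-required rule would also be valid, but the split costs about 8 to 10 percentage points of power at 92 per group, and the both-required rule needs a power calculation for pain.

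The cost is a few sentences and one real concession: pain, a main part of the rationale for the modified technique, cannot be claimed as confirmatory if continence fails. The choice should be recorded before any outcome data are examined.

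### The primary continence outcome is the Wexner state after surgery, with no described baseline score, new-onset definition or adjustment, so incontinence present beforehand cannot be told apart from incontinence caused by the technique

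*Protocol article*

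**What the plan says.** - **Outcome (section 2.5).** The continence outcome is "continence state after surgery as assessed with Wexner incontinence score". It is a postoperative state. Neither change from baseline nor new or worsened incontinence is mentioned.
- **Timing.** The Abstract says the outcomes "will be recorded at 1, 2, 3, 4 weeks, then every month in the outpatient clinic". Section 2.5 gives the same schedule: "Patients will be followed-up at 1, 2, 3, 4 weeks, then every month in the outpatient clinic". No preoperative time point is given for continence.
- **Preoperative work-up (section 2.4).** Before the operation, "patients will get blood routine test, blood glucose, coagulation, liver and kidney function, infectious disease test series, and electrocardiogram". A continence score is not listed.
- **Eligibility (section 2.2).** The surgical-history exclusion is "Patients who have undergone AF surgery 2 or more times", so a patient with one earlier fistula operation can enter. Incontinence is not named. The nearest criteria are the inclusion "Patients without obvious deformity of anus before the operation" and the exclusion "Patients with rectal cancer, rectal polyps, and other anorectal diseases".
- **Sample size (section 2.6).** The control rate comes from literature that "reported fecal incontinence to occur in up to 25.5% of patients with AF after cutting seton technique". The modified technique is assumed to give 10%. This leads to 92 per group, and 204 in total after allowing for loss to follow-up.
- **Analysis (section 2.7).** Continuous data get a t test or Mann–Whitney test, and categorical data a Fisher or chi-squared test. No covariate is named.

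**The concern.** The Introduction and Discussion attribute continence problems to the scar and sphincter damage that surgery leaves, and section 2.6 powers the trial on incontinence following each technique. The quantity of interest is therefore incontinence caused by the assigned operation. The outcome as defined is wider: it also counts a deficit that was present before surgery, including any left by the one earlier operation that eligibility permits.

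Such patients would be expected equally in both arms, so the comparison is not biased. What is at stake is precision and interpretation:

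- On the Wexner score, stable differences between patients add variance that an unadjusted test leaves in the error term.
- On the incontinence rate, prior cases count as events in both arms whatever the technique does. That narrows the difference and moves both rates towards 50%, where the variance is larger.

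Timing matters because a preoperative score can be collected only before the operation. A later analysis plan can add a covariate but cannot create the measurement.

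**Working it through.** **1. Reproduce the planned size.** Inputs from sections 2.6 and 2.7: p1 = 0.255, p2 = 0.10, two-sided α = 0.05, power 0.80. With the unpooled formula:

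n = (1.960 + 0.842)² × [p1(1−p1) + p2(1−p2)] / (p1−p2)²
= 7.849 × (0.1900 + 0.0900) / 0.155² = 91.5, rounded up to 92 per group.

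This matches the article. The pooled formula gives 95. The total of 204 is 102 per group, an implied loss of 1 − 184/204 = 9.8%.

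**2. Effect on the binary rate.** Let b be the share incontinent beforehand, equal in both arms and persisting. *Assumptions:* the article gives no value for b, so a range is shown; and 25.5% and 10% are taken as new-onset rates among the rest. The observed rates become

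q = b + (1−b)p, so the difference is (1−b) × 15.5 points.

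Power at 92 evaluable per group (pooled formula) is

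Φ{ [ (q1−q2)√92 − 1.960√(2q̄(1−q̄)) ] / √(q1(1−q1) + q2(1−q2)) }, with q̄ the mean of q1 and q2.

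| b (assumed) | Control vs modified | Difference (points) | Power at 92 | n per group for 80% |
|---|---|---|---|---|
| 0 | 25.5% vs 10.0% | 15.5 | 0.791 | 95 |
| 2% | 27.0% vs 11.8% | 15.2 | 0.745 | 106 |
| 5% | 29.2% vs 14.5% | 14.7 | 0.679 | 123 |
| 10% | 33.0% vs 19.0% | 14.0 | 0.579 | 154 |
| 15% | 36.7% vs 23.5% | 13.2 | 0.495 | 190 |

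At b = 5%, for example, q1 = 0.05 + 0.95 × 0.255 = 0.292 and q2 = 0.05 + 0.95 × 0.10 = 0.145. The smaller difference alone raises the required n by a factor of 1/0.95² = 1.11. The larger variance (0.331 against 0.280 for the sum of the two terms) raises it by a further 1.18.

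**3. Effect on the score.** A stable baseline deficit adds variance and does not by itself shrink the mean difference. Adjusting for a baseline that has correlation r with the outcome leaves a fraction 1 − r² of the variance. The article gives no r. At r = 0 nothing is gained. At an assumed r = 0.5 the remaining fraction is 0.75, so 184 evaluable patients carry the information of 184/0.75 = 245 analysed without adjustment.

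**The case against.** Several points on the other side stand, and they limit the conclusion.

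- **Silence on a baseline score is not proof that none is taken.** A reader might infer from the work-up list that continence is never scored before surgery. That list is visibly incomplete: section 2.4.1 relies on preoperative ultrasound or MRI, which the list omits. The recording times are also loose, since the Abstract puts operation time among the outcomes recorded at the follow-up visits. The article is condensed, and a fuller protocol may contain a baseline score. The outcome definition, however, is given here, and it is postoperative state.
- **Randomisation.** A reader might infer bias between the arms. With 1:1 random allocation (section 2.3) the unadjusted comparison is unbiased, and adjustment is a gain in efficiency.
- **Prior surgery.** A reader might infer that chance imbalance in earlier operations could not be corrected afterwards. The number of earlier operations must be known to apply the exclusion, so it can be adjusted for. Only baseline continence would be lost, and only if it is not recorded.
- **Eligibility.** The anal-deformity and other-anorectal-disease criteria may remove some incontinent patients. Neither names incontinence.
- **The power figures.** Section 2.6 does not say whether 25.5% counts only new cases. If it counts all postoperative incontinence, prior cases are already inside it and the table counts them twice. The range for b, full persistence and r = 0.5 have no source in the article.
- **Pain.** The same argument does not carry over to the pain outcome, which is defined as pain after tightening and so has no preoperative counterpart.

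**Conclusion.** The point holds as one of definition and efficiency. The primary continence outcome, as written, does not distinguish new or worsened incontinence from incontinence already present, and the stated tests make no use of a baseline.

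The size cannot be determined from the article. If the binary rate is the analysed outcome, if 25.5% and 10% are new-onset rates, and if 5% to 10% of patients are incontinent beforehand and stay so, power at 92 per group is about 68% to 58% instead of 79%. The plan has no spare power at 92, so even 2% would cost between 4 and 5 percentage points (0.791 to 0.745). If the score is analysed, the cost is lost precision that depends on the unknown baseline correlation. The documents support neither a claim of systematic bias nor one that this loss of power will occur.

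**What to change.** 1. Record the Wexner score at the existing preoperative assessment, or confirm that the full protocol already does so and say so in the outcome section.
2. Where continence is analysed as a rate, define the event as new or worsened incontinence relative to the preoperative score. State whether the cited 25.5% uses a comparable definition, so that the sample size and the event match.
3. Adjust the primary continence analysis for baseline Wexner and previous fistula surgery (none or one), with ANCOVA for the score and logistic regression for the rate.

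The cost is one short questionnaire per patient before surgery and a standard regression available in the software already named. No extra patients or visits are needed. The questionnaire has to be in place before further patients are operated on.
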